#### Economic evaluation

For the cost-effectiveness analysis, we will empirically quantify the incremental cost-effectiveness ratio (ICER) for the cost per additional facility-based delivery and per additional ANC visit. We will calculate the total healthcare expenditure during pregnancy, delivery, and neonatal period to calculate the incremental costs, which will be divided by the primary outcomes (i) facility-based delivery and (ii) ANC visits. Furthermore, we will calculate ICER with DALYs as denominator by using the standard DALY formula by limiting the disabilities caused by the most common and life-threatening obstetric complications (postpartum hemorrhage, obstructed labor, puerperal sepsis, preeclampsia/eclampsia, and asphyxia) [60–62]. In a second step, we will assess the robustness of the cost-effectiveness analysis by applying a sensitivity analysis. For the quantification of financial distress, we consider the cumulative number of patients reporting at least one of the following signs of financial distress due to maternal and neonatal healthcare costs: (i) assets sold or money borrowed, (ii) relative or friend asked to pay, (iii) catastrophic healthcare expenditure of more than 10% of annual household income, and (iv) essential healthcare forgone because of expected expenditure. All local costs will be calculated in Malagasy Ariary (MGA) before conversion to US dollars (USD) using the average annual exchange rate. Costs and health effects will be discounted and inflation-adjusted using the average consumer price index during the study period. We will use the market price for salary and utility grid to value the additional workload.

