### Analysis

#### Power calculation

For our baseline power calculation, we assumed a facility-based delivery rate of 67% and an average count of two ANC visits during pregnancy without the intervention [35]. The potential study population was approximately 10,000 pregnant women in the study region during the intervention period. We assumed that 50% of participants living in catchment areas of health facilities that received the intervention would adopt the MMHW. We calculated the minimum detectable difference between the intervention and control groups for the three primary outcomes using methods for cluster randomized trials. We assumed a 20% loss to follow-up and an intra-cluster correlation of 0.05. The intra-cluster coefficient (ICC) was conservative compared to ICCs that were empirically measured in similar settings [57]. Using the standard method for power calculations for binary outcomes, with a 95% two-sided confidence level, we would have 80% power to detect a 4-percentage point increase in the rate of facility-based deliveries, an 80% power to detect an increase of 0.08 average ANC visits per woman, and an increase of total health expenditure of 1700 Malagasy Ariary if we enrolled 2300 participants per group.

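### If the protocol's own detectable effects and ICC hold, the planned cost-effectiveness ratios would usually have no bounded 95% confidence set; net benefit should be pre-specified beside them

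*Protocol article*

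**What the plan says.** The Economic evaluation section commits to two ratios: "we will empirically quantify the incremental cost-effectiveness ratio (ICER) for the cost per additional facility-based delivery and per additional ANC visit". The numerator is the incremental total healthcare expenditure; the denominators are the effects on facility-based delivery and on ANC visits. A further ratio per DALY is planned. On uncertainty the section says only that "we will assess the robustness of the cost-effectiveness analysis by applying a sensitivity analysis"; it does not describe that analysis.

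Table 1 lists the cost per additional delivery and the cost per additional visit as registered secondary outcomes, but defines each the other way up, as the effect divided by the expenditure effect.

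The Power calculation gives the precision the trial expects. It uses these baseline values: "we assumed a facility-based delivery rate of 67% and an average count of two ANC visits during pregnancy without the intervention". It adds: "We assumed a 20% loss to follow-up and an intra-cluster correlation of 0.05". With 2300 women in each arm and a two-sided 5% test, it claims "80% power to detect a 4-percentage point increase in the rate of facility-based deliveries". The matching detectable differences for the other two primary outcomes are given as 0.08 visits and 1700 MGA.

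**The concern.** A ratio behaves badly when its denominator may be close to zero. A small estimated effect makes the ratio very large. A negative estimate reverses its sign, and a negative ratio can mean either cheaper and better or dearer and worse. A 95% Fieller set for cost divided by effect is unbounded exactly when the effect is not significant at the two-sided 5% level, so the question is how often that would happen here.

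Cost-effectiveness is a stated aim, and the Discussion says the results will inform the Ministry of Health on whether integrating the wallet into national programmes is beneficial. A ratio with no finite limits, or with an ambiguous sign, serves that purpose poorly.

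**Working it through.** **Inputs from the protocol.** Delivery 67% vs 71%; ANC effect 0.08 visits on a mean of 2; expenditure effect 1700 MGA; 2300 women per group; 20% loss; ICC 0.05 (all Power calculation). 61 facilities and 4600 women (Abstract). One enumeration area is sampled per facility (Population survey-based impact evaluation), so the cluster count stays at 61.

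**Step 1: the stated power.** Without clustering or loss, SE = sqrt[(0.67×0.33 + 0.71×0.29)/2300] = 0.0136. Power = Φ(0.04/0.0136 − 1.96) = 83.5%, and the detectable difference is 2.80 × 0.0136 = 3.8 points, which rounds to the stated 4. With 20% loss alone (1840 per group), power is 74.7%. The stated 80% is therefore matched only approximately, and only with clustering and loss left out.

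**Step 2: with the stated ICC.** Women per facility = 4600/61 = 75.4. Design effect = 1 + 74.4 × 0.05 = 4.72. SE = 0.0136 × sqrt(4.72) = 0.0296, or 2.96 points. At a true 4-point effect z = 0.04/0.0296 = 1.35 and power is 27%.

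**Step 3: the delivery ratio.** P(unbounded) = P(|z| < 1.96) = 1 − 0.27 = 73%. P(estimate ≤ 0) = Φ(−1.35) = 9%. After 20% loss (60.3 women per facility, design effect 3.97, SE 3.03 points) P(unbounded) is 74%. A cluster-level simulation with 32 and 29 facilities gave 73-74%.

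| True delivery effect | ICC | P(unbounded), 4600 women |
|---|---|---|
| 4 points | 0.05 | 73% |
| 6 points | 0.05 | 46% |
| 8 points | 0.05 | 21% |
| 4 points | 0.01 | 40% |
| 4 points, stated 80% power taken as true | – | 20% |

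At ICC 0.05 the figure passes below 50% at an effect of about 5.7-5.9 points. At a 4-point effect it passes below 50% once the ICC is under about 0.013-0.017.

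**Step 4: the ANC ratio.** The protocol gives no SD of visits, so a range is assumed. Solving 0.08/2.80 = SD × sqrt(2/n) gives 0.97 for n = 2300 and 0.87 for n = 1840; a variance equal to the mean of 2 gives 1.41. With SE = SD × sqrt(2 × 4.72/2300), the SEs for SDs of 0.87, 0.97 and 1.41 are 0.056, 0.062 and 0.091. P(unbounded) is 70%, 75% and 86%.

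**Step 5: the Table 1 direction.** With expenditure as the denominator, and an SD of about 18,400-20,600 MGA solved in the same way from 1700 MGA, P(unbounded) is 70-76%. Turning the ratio over does not help.

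**Step 6: spread of the ratio in MGA (illustration only).** Dividing the two detectable differences gives 1700/0.04 = 42,500 MGA. The cost SE is assumed: 1700/2.80 = 607 unclustered, and 607 × sqrt(4.72) ≈ 1319 clustered. With the clustered value, the central 95% of simulated ratios runs from roughly −330,000 to +450,000 MGA at zero cost-effect correlation, and from about −95,000 to +195,000 at correlation 0.8.

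**The case against.** The strongest reply has four parts.

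- **An ICER is a standard summary, and the article excludes no interval method.** A bootstrap, a Fieller interval or an acceptability curve may be in an analysis plan that is not shown. This stands: the absence of a named interval method is not the point. A reader might also infer that the planned sensitivity analysis only varies inputs. The text does not say so, and a resampling analysis would fit its wording.
- **The 73% is simply 1 minus power.** This also stands. The cause is the Power calculation, and the figure should not be counted as a second, independent defect of precision.
- **A reader might infer that the ratio fails in most trials whatever the truth.** The documents do not support that. The 4 points are a detectable difference, not a forecast, and the ICC is described as conservative; the table above shows how quickly the figure falls with a larger effect or a lower ICC.
- **Net benefit uses the same noisy differences.** Correct. With the effect SE of 0.0296 and an uncorrelated cost SE of 607, net benefit at a value λ of 200,000 MGA per delivery is 200,000 × 0.04 − 1700 = 6300. Its SE is sqrt[(200,000 × 0.0296)² + 607²] ≈ 5950, so power to show it positive is about 18%. It is about 12% at λ = 100,000 and 25% at 1,000,000, and stays at or below about 27%. Nobody should expect it to settle the question.

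What remains is that the ratio can have no finite limits and an ambiguous sign, while net benefit from the same women's data always has a finite interval and one direction of reading.

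**Conclusion.** The point holds in a conditional form. At the protocol's own detectable differences and ICC of 0.05, the 95% Fieller set is unbounded in about 73% of trials for delivery and about 70-86% for ANC visits. The delivery result uses only the protocol's figures; the ANC result also needs an assumed SD. With a true delivery effect above about 6 points, or an ICC near 0.01, an unbounded set is no longer the usual outcome.

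The MGA range carries less weight, because both the cost SE and the cost-effect correlation are assumptions. The unbounded probabilities for the Economic evaluation ratios do not depend on either. Choosing an ICER is not an error in itself. The weakness is that the ratio is the only form of result fixed in the article, at a precision where it may often be unreadable.

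**What to change.** Keep the registered ICERs as point estimates. Pre-specify beside them:

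- incremental net benefit per woman, λ × outcome − cost, regressed on assignment with facility clustering and strata, over a stated range of λ;
- a facility-level bootstrap of the joint cost and effect differences, with an acceptability curve;
- a rule to state the quadrant (dominant, dominated or trade-off) whenever the ratio is negative or the effect interval includes zero.

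Reconcile the direction of the ratios between Table 1 and the Economic evaluation section. The power statement itself needs its own correction, which this change does not supply.

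The cost is wording and code: expenditure, delivery and ANC visits are already collected on the same women, and outcome collection was to start only on January 1, 2022. The downside is that results must be read over a range of willingness to pay, since no agreed value per delivery or visit is stated.

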#### Data analysis qualitative data

All qualitative interviews will be digitally recorded, verbatim transcribed, and translated by trained scientists. We will adopt in vivo coding, with codes, categories, and themes emerging as we proceed through the data, although the initial coding process will be guided by the specific research questions. This approach will ensure that we pay attention to emerging interpretations of the data, while ensuring fidelity to the initial research question. Strategies to isolate themes will include identifying repetition, typologies, and categories grounded in the data, transitions, similarities and differences, linguistic connectors, missing data, and theory and research question-related material [63]. We will compare information across data sources, checking for consistency in the interpretation. At least two researchers will code and interpret each set of data independently on the basis of a jointly developed and validated codebook. The final interpretation of the findings will be discussed among the entire study team. We will rely on current software applications for support during the coding and analysis process.

#### Data and safety monitoring

To monitor data quality and safety, the aggregate data for each outcome will be analyzed continuously during data collection after the trial period. An independent data and safety monitoring board (DSMB) will assess adherence to the protocol, safety of participants, and progress of the trial as well as data quality and completeness. The board includes two Madagascar- and two Germany-based scientists. In a closed session, the DSMB will be provided with data by the study team’s statistician on each outcome disaggregated by assignment to intervention or control group. All protocol amendments will be communicated directly to the Ethics Committee and trial registries by the project management group, consisting of the principal investigator and the Malagasy study director, as well as the DSMB, and further to the trial participants via the investigators. There are no stopping rules for this trial because it is unlikely that the intervention could lead to adverse effects and the control consists in no additional intervention.

#### Confidentiality

Both primary and secondary data will be stored and handled according to the European Union General Data Protection Regulation guidelines. At the point of data collection, codes based on a series of characteristics will be assigned to participants to maintain participants’ confidentiality. A master sheet linking the code with identifying information, including a name and, when feasible, contact information, will be kept in a secure password-protected online repository that is accessible only to the investigators. Only the principal investigator will have access to and manage this master sheet. The master sheet will facilitate the process of revoking information should a participant decide at a later to have their data removed from the study.

## Discussion

The 4MOTHERS hybrid effectiveness-implementation type-1 trial described in this protocol is the first to determine the causal impact of the MMHW, a mobile money-based savings and payment service, on maternal and neonatal health outcomes and financial access to healthcare. In addition, the trial will gather information on the implementation of the intervention. The quantitative and qualitative research produced from this study will help to understand the economic, social, and behavioral impact of the MMHW in a low-resource public healthcare setting. Furthermore, an economic evaluation will serve to determine the cost-effectiveness of the intervention and to model the costs for its future implementation. Among the strengths of this study is that the intervention was developed based on a human-centered design study harnessing the experiences and recommendations of target communities and key stakeholders by soliciting their feedback on the design of the intervention [41]. Furthermore, the focus on rigorous scientific methodology in a real-world setting including urban, peri-urban, and rural populations and the integration of the trial within the public health system of Madagascar will ensure high applicability and transferability of results to communities in other LMICs. In addition, the rapidly growing penetration of MM services, mobile communication, and other digital technologies and the increasing general tech-savviness in LMICs yield promising pathways for disseminating and scaling the intervention to other under-resourced communities.

The 4MOTHERS trial has several limitations. First, the catchment areas of participating public-sector health facilities selected for the population-based survey are randomly distributed throughout the study region. This creates many boundary areas between intervention and control facilities, which can lead to possible contamination bias should women who live in the catchment area of a control health facility inadvertently be exposed to the intervention, thus potentially minimizing the difference in outcomes between the two groups. Thus, to adjust for contamination bias, we will conduct a CA ITT analysis. Second, the trial takes place in a real-life setting where normal service delivery and targets have to be ensured by participating health facilities alongside the trial intervention, which might impact the adoption of the intervention by health workers. Third, the particular design of the MMHW may impact the uptake and efficiency of the intervention. The trial thus has to be considered as a test of the MMHW “in real life,” and we cannot necessarily conclude from a null finding that mobile money-based savings and payment service for maternal healthcare cannot be effective in another context. Fourth, women who receive the intervention will be entitled to conditional cash transfers and electronic vouchers for free ANC drugs, prenatal ultrasound exams, and emergency evacuation to a reference hospital, which may have an independent effect on maternal and neonatal health outcomes. Therefore, the results of the study can only be considered for the intervention as a whole and should not be reduced to MMHW alone. However, they should be interpreted in the context of effective delivery of conditional cash transfer and electronic vouchers as an inherent strength of the MMHW.

Taken together, we expect that the results of the 4MOTHERS trial will guide future policy decisions and digital health interventions related to improving maternal and neonatal health outcomes and UHC in Madagascar and other countries in SSA. In particular, the results of this trial will inform the Malagasy Ministry of Health and government stakeholders in other countries in SSA whether the integration of the MMHW within national programs is a feasible and beneficial health systems intervention. We will disseminate our results via peer-reviewed journals and presentations at scientific conferences and continuously engage with our policy partners during the operationalization of this trial and as results emerge.

### Trial status

Implementation of the intervention package at all participating public-sector health facilities of the intervention group has been completed in May 2020. The intervention is ongoing. Participants who completed their pregnancy between July 1, 2020, and December 31, 2021, will be enrolled for the randomized outcome assessment starting on January 1, 2022 (Fig. 2). Protocol version: 1.0; issue date: February 15, 2020.

## Data Availability

The findings of this study will be shared with the Malagasy Ministry of Health. In addition, the full protocol and participant-level anonymized data will be made publicly available using an open data repository. The results of the study will be published in peer-reviewed journals and presented at conferences.

## Abbreviations

4MOTHERS: Madagascar mobile money for maternal healthcare related spending
ANC: Antenatal care
CHW: Community health worker
DALY: Disability-adjusted life year
DSMB: Data and safety monitoring board
GSM: Global system for mobile communication
ICER: Incremental cost-effectiveness ratio
IV: Instrumental variable
LMICs: Low- and middle-income
MGA: Malagasy Ariary
MMHW: Mobile maternal health
MM: Mobile money
OOP: Out-of-pocket
SPIRIT: Standard protocol items: recommendations for interventional trials
SSA: Sub-Saharan Africa
TAN: Transaction authentication number
UHC: Universal health coverage
USD: US Dollars
USSD: Unstructured supplementary service data
WHO: World health organization
